**Research Project Submission Form**

**A. Identification details:**

| **Code No.** (To be filled by the Research cell): |
| --- |
| **Type of project**: Intramural [�] Extramural [ ]  Drug trial/devise [ ] Collaborative [ ] Other [ ]  **Status of review**: New [�] Revised [ ]  **Proposal Title:** “Safety and efficacy of antiviral therapy alone or in combination in symptomatic patients of Covid-19 infection - a randomised controlled trial (SEV-Covid Trial)”  **Full Title of the Trial:** “Safety and efficacy of antiviral therapy alone or in combination in symptomatic patients of Covid-19 infection - a randomised controlled trial (SEV-Covid Trial)” |

**C. Sponsor Information: Applicable [ ] Not applicable [**�**]**

| 1. **Name of sponsor/CRO:** |
| --- |
| 1. **Indian: a) Government** ⬜ Central ⬜ State ⬜ Institutional ⬜   **b) Private** ⬜ |
| 1. **International:** Government ⬜ Private ⬜ UN Agencies ⬜ |
| 1. **Industry:** National ⬜ Multinational ⬜ |
| 1. **Contact address of sponsor/CRO:** |
| 1. **Budget: Rs._____________________** 2. **Details of allocation of budget in Clinical Trial Agreement:** Yes [ ] No [ ] |

**D. Study related Information:**

| 1. **Design of study:** Epidemiological ⬜ Basic Sciences ⬜ Behavioral ⬜   Clinical ⬜ Interventional � ✔ Single Centre ⬜ Multicentre ⬜ |
| --- |
| 1. **No. of participants: AIIMS, Rishikesh Total (if multicentre)**   **Patient total = all patients who presented within the study period**  **Control**   1. **Duration of study: 6 months** 2. **Duration of subject participation (no. of visit by a participant in study): 28 days OR till patient is discharged or death whichever is longer ✔** |

**E. Interventional study: Yes [**�✔**] No [ ] If No, move to next section i.e. F**

| 1. **Does the study involve use of?**   Drugs ✔✔ Devices ⬜ Vaccines ⬜ Radiopharmaceutical ⬜  Recombinant DNA/Gene therapy ⬜ Stem cell ⬜ *(need BARC approval)*  *(need DBT-* *GEAC approval (NAC-SCRT registration and approval)*  Indian Systems of Medicines/ Alternate systems of Medicine ⬜  Any Other ⬜ None ⬜ |
| --- |
| 1. **Is it approved and marketed?**   In India �✔ UK & Europe � USA � Other Countries, Specify_______ |
| 1. **Does it involve a change in use, dosage, route of administration?** ✔ Yes ⬜ No   **If yes,** whether DCGI’s/Any other Regulatory Authority’s Permission is obtained?  Yes ⬜ No ⬜ ✔  **If yes,** copy of permission attached. Yes ⬜ No ⬜ |
| 1. **Is it an Investigational New Drug?** Yes ⬜ No � ✔   **If yes**   1. Investigator’s Brochure enclosed Yes ⬜ No ⬜ 2. Preclinical studies data available (If yes, provide summary) Yes ⬜ No ⬜ 3. Clinical studies data available (If yes, provide summary) Yes ⬜ No ⬜ 4. Clinical study is Phase I ⬜ Phase II ⬜ Phase III ⬜ Phase IV ⬜ NA ⬜   **If phase I-III** will the drug/device be provided free? Yes ⬜ No ⬜  **If phase IV** will the drug/device be provided at cost less than Yes ⬜ No ⬜  Hospital pharmacy?   1. DCGI’s permission obtained Yes ⬜ No ⬜   **If yes,** copy of letter enclosed Yes ⬜ No ⬜   1. Registered with Clinical Trial Registry – India Yes ⬜ No ⬜ 2. If yes copy of certificate enclosed Yes ⬜ No ⬜ |
| 1. **Data monitoring** 2. Is there a plan for reporting of adverse events? Yes ✔� No ⬜   **If yes**, reporting will be done to Sponsor ⬜ IEC � ✔   1. Is there a plan for interim analysis of data? Yes✔ � No ⬜ |
| 1. **Provision for travel/treatment due to injury out of study** Yes ⬜ No � ✔   **If yes**, by Sponsor ⬜ Investigator ⬜ Insurance Company ⬜ Any Other ⬜ |

**F. Details of participant of study:**

| **1. Will subjects from both sexes be recruited:** Yes [�✔] No [ ] |
| --- |
| 1. **Inclusion/exclusion criteria given:** Yes [�✔] No [ ] |
| 1. **Type of subjects:** Volunteers [] Patients [�✔ ] |
| 1. **Vulnerable subjects** Yes [ ] No [�✔]   (if **Yes** tick the appropriate boxes)  Pregnant Women [ ] Children [ ] Elderly [ ] Foetus [ ]  Illiterate [ ] Handicapped [ ] Terminally ill [ ] Seriously ill [ ]  Mentally challenged [ ] Economically & socially backward [ ] Any other [ ] |
| 1. **Special group subjects:** Yes [ ] No [�✔]   ( if **Yes** tick the appropriate boxes)  Captives [ ] Institutionalized [ ] Employees [ ] Students [ ]  Nurses/Dependent [ ] Staff [ ] Armed Forces [ ] Any Other [ ] |

G. **Privacy and confidentiality:**

| 1. **Study Involves** Direct Identifiers (Pt. identified by name/Cr. no.) ✔ �   Indirect Identifiers/Coded (Pt. identified after break of code) ⬜  Completely Anonymised /Delinked (Pt. cannot identified) ⬜   1. **Confidential handling of data by staff** Yes✔ � No ⬜ |
| --- |

**H. Detail of sample collection (If no sample being collected, move to next section i.e. I):**

| **A. *Regarding sample collection: NA***   1. **Collection of organs or body fluids or blood. If yes, please specify** Yes ✔ No ⬜   **Type: BLOOD**  **Amount each time: 06ml**  **No. of time: Every 72 hours**   1. **Collection of fetal tissue or abortus. If yes, please specify** Yes ⬜ No ⬜ 2. **Use of pre-existing/stored/left over samples. If yes, please specify** Yes ⬜ No ⬜   **____________________________________________________________________________________________________________________________**   1. **Proper disposal of material** Yes ⬜ No ⬜   ***B. Special situation***   1. **Will any sample collected from the patients be sent abroad?** Yes ⬜ No�   If yes, give details and address of collaborators  **______________________________________________________________**   1. ***Sample will be sent abroad because (Tick appropriate box)***   Facility not available in India ⬜  Facility in India inaccessible ⬜  Facility available but not being accessed ⬜  If so,reasons_________________________________________________________________   1. ***Has necessary clearance been obtained*** Yes ⬜ No ⬜ 2. **Collection for banking/future research** Yes ⬜ No ⬜ |
| --- |

1. **Participant Information Document (PID) and Consent Form:**

| 1. **Consent** *Written � ✔ Oral ⬜ Audio-Visual ⬜   Patient Information documents and consent form attached : (Tick the included elements)  Understandable language � Alternatives to participation �  Statement that study involves research � Confidentiality of records �  Sponsor of study � Contact information �  Purpose and procedures � Statement that consent is voluntary�  Risks & discomforts � Right to withdraw �  Benefits � Benefit if any on future �  Consent for future use of material biological NA  Free supply of drug till it is not marketed in country if necessary: NA  Compensation for study related injury: NO  Translation of Participant Information Document (PID) in local Language   1. **If healthy volunteers, PID for them NA** Yes No ⬜ 2. **If participant is child, PID for parent** : NA Yes ⬜ No ⬜ 3. **PID and Assent Form for child 8-18 yrs: NA** Yes ⬜ No ⬜ 4. **Consent form** in English � Local Languages �   (For participant/healthy volunteer/parent/legal guardian)   1. **Who will obtain consent?** PI-Co-PI � Nurse/Counselor ⬜   Research Staff ⬜ Any Other ⬜  ****If written consent is not obtained, give reasons……………………………………………...*** |
| --- |

| 1. **Will any advertising be done for recruitment of Subjects?** Yes ⬜ No �   (Posters, flyers, brochure, websites – if so attach a copy) |
| --- |

| 1. **For archival of record by Research Review cell for more** Yes ⬜ No � Not applicable ⬜   **than 5 years required**  If yes, for how many years……………………… |
| --- |

1. **Risk and benefits:**

| 1. **Is there physical/social/psychological risk/discomfort?** Yes ⬜ No �   **If yes**, Minimal or no risk ⬜  More than minimum risk ⬜  High risk ⬜   1. **Is there benefit** a) to the subject? Yes � No ⬜   Direct � Indirect ⬜  b) to the society Yes � No ⬜   1. **Do you think that the risk is in commensurate with the benefits to be accrued subjects/community/country?** Yes � No ⬜ 2. **Please identify the ethical issues involved in your study:** 3. High dose of chloroquine may have adverse effects; however, adverse effect monitoring will be done regularly. |
| --- |

| 1. **Do you have conflict of interest?** Yes ⬜ No �   **(Financial/Non financial)**  **If yes**, specify________________________________________________________________ |
| --- |

1. **Brief description of the proposal**

|  | Title of the project: **“Safety and efficacy of antiviral therapy alone or in combination in symptomatic patients of Covid-19 infection - a randomised controlled trial (SEV-Covid Trial)”** |
| --- | --- |
| (a) | Aim: To assess the safety and efficacy of Antiviral Therapy In Symptomatic Patients of COVID-19 Infection |
| (b) | Objectives:   1. To compare the safety and efficacy of Hydroxychloroquine with Ribavirin and standard treatment in patients of non-severe COVID-19 infection 2. To compare the safety and efficacy of standard treatment, Lopinavir-ritonavir with Ribavarin, and Hydroxychloroquine with Ribavirin in patients of severe COVID-19 infection |
| (c) | **Justification for study**: COVID 19 infection had become a pandemic. The presentation of the disease is highly variable. The treatment options for the disease are limited at present. For non-severe patient’s supportive treatment forms the mainstay of management. Various regimens have been tried in critically ill patients. Hydroxychloroquine, Lopinavir-ritonavir combination has been tried in clinical trials with limited success. The present study is planned to explore the combination of the above drugs with Ribavirin in different categories of COVID-19 infection. |
| (d) | **Scope of the Project**: The present study will evaluate the therapeutic potential of Hydroxychloroquine and Lopinavir-ritonavir in combination with Ribavirin in symptomatic cases of COVID-19 infection in a tertiary care hospital in India |
| (e) | Details of procedure and methodology proposed to be used (300 words) including description of the potential risks and benefits, exclusion and Inclusion criteria outcome measures, statistical analysis:  ***Patient population:*** *Covid-19 positive symptomatic cases either non-severe or severe category*  ***Intervention:*** *Two therapeutic interventions for non-severe category and three for severe category as described below*  ***Comparator:*** *Parallel arm design, compared among other interventional arm in same category*  ***Outcomes:*** *Clinical and laboratory improvements in 72 hours of treatment*  **Patient population-**  Patients diagnosed with SARS-CoV-2 infection after positive reverse-transcriptase–polymerase chain reaction (RT-PCR) assay.  **Inclusion criteria:**   1. Age ≥18 years at time of participation in the study 2. Laboratory (RT-PCR) confirmed infection with SARS-CoV-2 3. Symptomatic (severe or non-severe) Covid-19 disease 4. Willingness of study participant to accept randomization to any assigned treatment arm   **Exclusion criteria:**   1. Use of medications that are contraindicated with Lopinavir/Ritonavir, Hydroxychloroquine/Chloroquine, or Ribavirin and that cannot be replaced or stopped 2. Patient already on antiretroviral therapy with Lopinavir-Ritonavir based regimen or on Hydroxychloroquine/Chloroquine or on Ribavirin 3. Any known contraindication to test drugs such as retinopathy and QT prolongation 4. Known allergic reaction or inability to delivery oraly to Lopinavir-ritonavir, Hydroxychloroquine/ Chloroquine, Ribavarin 5. Pregnant or breastfeeding females 6. Receipt of any experimental treatment for 2019-nCoV (off-label, compassionate use, or trial related) within 30 days prior to participation in the present study or want to participate after enrolment   **Potential benefits:**   1. All those who participate in the trial will benefit from possible effective treatment for COVID-19 infection 2. The study will highlight the therapeutic options in management of the symptomatic patients of COVID-19 infection   **Potential risks:**  The present study will be conducted on symptomatic patients of COVID-19 attending AIIMS Rishikesh. The patients will be categorised based on severity and treatment will be allocated accordingly.  Adverse drug reactions, though not frequent may be associated with the treatment. Proper supportive management will be given to the patients at the institute.  **Methodology**:  **Flow Diagram**  Patients of COVID-19 infection - After confirmation by RT-PCR at AIIMS, Rishikesh  Screening for inclusion in trial Enrolment Excluded  ♦  Not meeting inclusion criteria  ♦  Declined to participate  ♦  Other reasons  Categorisation based on severity of patient  **SEVERE group**  **NON-SEVERE group**  Randomisation to treatment arm:  **A. Standard Treatment (ST-S)**  **B. Hydroxychloroquine + Ribavirin + ST-S**  **C. Lopinavir+ Ritonavir + Ribavirin + ST-S**  Randomisation to treatment arm:   1. **Standard Treatment (ST-NS)** 2. **Hydroxychloroquine + Ribavirin + ST-NS**  RandomisationAllocation Monitor progress of patient in 72 hours Follow-Up Patient improve- continue same treatment  Clinical evaluation- @72 hours  Improve - Continue same treatment  Progress – achieved end point and Shift to institute protocol for further treatment  Patient do not improve/ Signs of severe disease  Shift to **SEVERE group** treatment arms after randomization with new consent Analysis Analysis  **Total duration of observation**:  28 days from the time of enrolment into the study OR till patient is discharged or death whichever is longer  **Design:** Open label, Parallel arm design, stratified randomised controlled trial:  Patients will be screened for the study after diagnosis of COVID-19 infection by Microbiology team. Patients will be categorised as non-severe or severe based on predefined criteria. The patient will be enrolled in the study after a written informed consent. Since it is an exploratory trial as COVID-19 being a new disease, all patients who came under the purview of the inclusion criteria within the study period and who have consented for the study will be included. Clinical evaluations will be done by a separate investigator. Blinding will not be performed but dynamic randomization will be done. Patients will be followed up for a period of 28 days from the day of enrolment.  At the time of enrolment, demographic information will be collected from participants, and relevant data on their medical histories, comorbidities, and risk factors for severe COVID-19. It will be documented along with investigations including CBC, ECG, LFT, RFT, G6PD status.  The patients will be categorised as severe based on the following criteria:   - Confirmed pneumonia on chest imaging, SPo2 <93%, Pao_2_:Fio_2_ <300 mg Hg - Respiratory failure (need of mechanical ventilation) - Septic shock - Multiple (>2) organ dysfunction syndrome (MODS) - Liver disease (Child Pugh score ≥ C, AST>5 times upper limit) - Patients with known renal impairment (estimated glomerular filtration rate ≤30 mL/min/1.73 m2) or receiving continuous renal replacement therapy, haemodialysis, peritoneal dialysis - Other single organ failure (e.g. heart, pancreas, etc) if specific definition meets   Non-severe category includes mild and moderate disease severity category other than severe ones.  **Treatment Schedule**  **Non-severe Treatment arms (NS-group):**   \| **Treatment Arm** \| **Drug** \| \| --- \| --- \| \| A \| Standard Treatment (ST_NS_) \| \| B \| Hydroxychloroquine 400 mg twice on first day followed by 400 mg per oral daily for 10 days + Ribavirin (2.4 g orally as a loading dose followed by 1.2 g orally every 12 hours) for 10 days + Standard Treatment (ST_NS_) ^6^ \|   **Standard Treatment for non-severe cases (ST_NS_):**   1. Strict Isolation 2. Standard Precautions (Hand hygiene, Cough Etiquette, Wear surgical mask) 3. Hydration 4. Proper Nutrition 5. Supportive Pharmacotherapy (Antipyretic, Antiallergic, Cough Suppressant) 6. Treatment of Comorbid Diseases 7. Oseltamivir (75 mg BD) for patient who are tested positive for H1N1   If the patient improves clinically the same treatment will be continued. If the patient do-not improve or shows sign of severity (mentioned above) the patient will be shifted to the severity arm (S-group) of the clinical trial and again randomization will be done and enrolled after new consent only for severe group. However, if intervention falls on HCQ arm, then it will be taken as end point reached and shifted to institute treatment protocol for further management.  **Severe group Treatment arms (S-group):**   \| **Treatment Arm** \| **Drug** \| \| --- \| --- \| \| A \| Standard Treatment (ST_s_) \| \| B \| Hydroxychloroquine 400mg BD on day1 followed by 400 mg once daily + Ribavirin (2.4 g orally as a loading dose followed by 1.2 g orally every 12 hours) for 10 days + Standard Treatment (ST_s_) \| \| C \| Lopinavir(400mg) + Ritonavir (100mg) two tablets twice daily+ Ribavirin (2.4 g orally as a loading dose followed by 1.2 g orally every 12 hours) for 10 days + Standard Treatment (ST_s_)^6^ \|   **Standard Treatment for severe patients: (ST_s_)**   1. Strict Isolation 2. Standard Precautions (Hand hygiene, Cough Etiquette, Wear surgical mask) 3. Fluid Therapy 4. Supportive Pharmacotherapy (Antipyretic, Antiallergic, Cough Suppressant) 5. Oxygen supplementation (As required) 6. Invasive ventilation (As required) 7. Antibiotic agents for other associated infections (according to 2019 ATS/IDSA guidelines for non-ICU and ICU patients) 8. Vasopressor support 9. Renal-replacement therapy 10. Treatment of Comorbid Diseases 11. Oseltamivir (75 mg BD) for patient who are tested positive for H1N1   Patients will be assessed for clinical and laboratory improvements in 72 hours of treatment. In case the patient does not respond to the current treatment regimen the patient will be shifted to institute protocol for current practice of treatment.  **Timelines of investigations: Repeated at 72hrs interval**   \| Investigations \| Baseline \| Next 72hrs \| \| --- \| --- \| --- \| \| CBC \| **✔** \|  \| \| LFT \| **✔** \|  \| \| KFT \| **✔** \|  \| \| HBA1C and Blood sugar \| **✔** \|  \| \| RT-PCR for SARS-Cov-2 (until 24hrs apart twice negative) \| **✔** \|  \| \| PT/INR \| **✔** \|  \| \| Serum Electrolytes \| **✔** \|  \| \| ABG \| **✔** \|  \| \| Chest Xray \| **✔** \|  \| \| ECG \| **✔** \|  \| \| Other organ markers as per involvement \| **✔** \|  \|     **Dose Modifications:**  If any serious adverse event is recorded, the participant will be withdrawn from the trial and management will be done accordingly as per institute policy.  **Recording adverse events:**  All adverse events will be recorded in the medical records in the first instance. All adverse events will be recorded with clinical symptoms and accompanied with a simple, brief description of the event, including dates as appropriate. Each adverse event will be assessed for severity, causality, seriousness and expectedness and informed to IEC within 24hours.  **Discontinuation/withdrawal of participants:**  A participant may be withdrawn from trial treatment whenever continued participation is no longer in the participant’s best interests, but the reasons for doing so must be recorded.  Reasons for discontinuing treatment may include:   1. Unacceptable drug toxicity 2. Development of progressive disease 3. Patients withdrawing consent to further trial treatment   **Endpoints:**  **Primary endpoints:**   1. Time to Clinical recovery (TTCR)    - TTCR is defined as the time (in hours) from initiation of study treatment (active or placebo) until normalisation of fever, respiratory rate, and oxygen saturation, and alleviation of cough, sustained for at least 72 hours.    - Normalisation and alleviation criteria: 2. Fever - ≤36.9°C or -axilla, ≤37.2 °C oral 3. Respiratory rate - ≤24/minute on room air 4. Oxygen saturation - >94% on room air 5. Cough- mild or absent on a patient reported scale of severe, moderate, mild, absent 6. Time to SARS-CoV-2 RT-PCR negative in upper respiratory tract specimen 7. Time to laboratory recovery of each organ involvement   **Secondary Endpoints:**   1. All causes mortality 2. Frequency of respiratory progression  - Defined as SPO2≤ 94% on room air or PaO2/FiO2 <300mmHg and requirement for supplemental oxygen or more advanced ventilator support.  1. Time to defervescence (in those with fever at enrolment) 2. Frequency of requirement for supplemental oxygen or non-invasive ventilation 3. Frequency of requirement for mechanical ventilation 4. Frequency of serious adverse events as per AIDS table grade of severity   **Statistical analysis**:  All COVID-19 positive patients will be included in the study after informed consent. Since it is an exploratory trial as COVID-19 being a new disease, all patients who came under the purview of the inclusion criteria within the study period and who have consented for the study will be included. Data will be described as mean+ SD for most of the parameters. Comparisons of the descriptive variables of the two arms will be performed using the Wilcoxon rank sum test for continuous variables and the chi-square or Fisher’s exact test for categorical variables. Primary analysis will include all patients (Intention to treat) and sub-group populations (per-protocol).  **Ethical clearance:**  The present study deals with a new infectious disease which has no definite treatment. Current therapy is based on symptomatic treatment. The present study explores the possibilities of new drugs in SARS-CoV-2 infection. The study will be conducted after IEC approval. Written informed consent will be taken from all participants.  **Safety Outcomes**  Safety outcomes will be determined according to the division of AIDS table for grading severity of adult adverse events (<https://rsc.niaid.nih.gov/clinical-research-sites/daids-adverse-event-grading-tables>), with specific focus on the events of gastrointestinal tract, arrhythmias, myopathies. In case of serious ADRs including death, compensation will be given as per institute protocol. |
| *(f)* | *Detailed time line for the project:(details of duration required for procurement, data collection, analysis, preparation of final report,etc)*  Duration of procurement: None, already available  Data collection: 5 months  Analysis: 15 days  Preparation of final report: 15 days |
| (g) | Resume of relevant literature on the subject, with special reference to the areas in which information is lacking:  COVID-19 is an infectious disease caused by novel corona virus SARS-CoV-2. WHO has declared it as a pandemic.^[[1]](#footnote-1)^ The presentation of the disease ranges from asymptomatic to mild cough, fever and sore throat. Disease can occasionally progress to pneumonia with acute respiratory distress syndrome, sepsis and septic shock. Definitive treatment is not available for COVID-19 infection. Strict isolation, standard precautions like hand hygiene and cough etiquette along with supportive therapy forms the mainstay of management. Antibiotics has been used as a part of standard treatment. Supportive treatment forms the mainstay of non-severe cases of COVID-19 infections. Hydroxychloroquine (HCQ) is thought to be effective in treatment and prophylaxis.^2^ Global consensuses on its use has been discussed widely.^3^ Lopinavir-ritonavir combination has also been tried in hospitalised patients.^4,5^ Combination of both the regimens with Ribavirin seems to be a potential therapeutic option in symptomatic COVID infections.^6,7^ Several combination therapies have also been suggested in the newly published literature. No clear consensus or definitive treatment is present till date. The present study explores therapeutic options in symptomatic patients with COVID-19 infection. |

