**BUDGETARY REQUIREMENT:**

| Details of items with quantity | Study period (6 Months) | Total (Rs) |
| --- | --- | --- |
| Manpower | 1 SRF (Senior Resident, Department of Pharmacology)  1 JRF (Junior Resident, Department of General Medicine) | Nil since he/she is part of institute resident-ship |
| Study drugs | Available in the institute |  |
| Equipment | Available in the institute |  |
| Investigations: n= any till end of the study  ECG (Baseline, every 72 hours)  LFT (Baseline and every 72 hours)  KFT (Baseline and every 72 hours)  CBC (Baseline and every 72 hours)  Others specific marker of an organ involvement | Available in the institute |  |
| Chemicals/ Reagents/ Consumables | Available in the institute |  |
| Contingencies | NA |  |
| Total |  |  |

Note: -

1. All expenditure should be logically justified by the proposed project
2. All purchases will be made as per GFR and institutional financial guidelines for research projects.

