**DEMOGRAPHICS**

| Sex at Birth ☐Male ☐Female ☐Not specified Date of birth: [__][__]/[__][__]/[__][__][__][__]  If date of birth is unknown, record: Age [___][___][___]years  Healthcare Worker? ☐Yes ☐No ☐Unknown  Laboratory Worker? ☐Yes ☐No ☐Unknown  Pregnant? ☐Yes ☐No ☐Unknown ☐N/A If yes: Gestational weeks assessment [___][___] weeks |
| --- |

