**LABORATORY RESULTS ON ADMISSION (*record units if different from those listed)**

| Parameter | Value | Not done | Parameter | Value | Not done |
| --- | --- | --- | --- | --- | --- |
| Haemoglobin (g/L) |  |  | Urine R/M (significant if any) |  |  |
| WBC count (x109/L |  |  | Sodium (mEq/L |  |  |
| Haematocrit (%) |  |  | Potassium (mEq/L) |  |  |
| Platelets (x109/L) |  |  | Calcium(mg/dL) |  |  |
| APTT/PT/INR |  |  | Lactate (mg/dL) |  |  |
| Total bilirubin (mg/dL) |  |  | Procalcitonin (ng/mL) |  |  |
| Direct bilirubin (mg/dL) |  |  | CRP (mg/L) |  |  |
| Albumin (g/dl) |  |  | LDH (U/L) |  |  |
| Globulin (g/dl) |  |  | Creatine kinase (U/L) |  |  |
| SGOT/SGPT (U/L) |  |  | Troponin (ng/mL) |  |  |
| Urea (mg/dL) |  |  | ESR (mm/hr) |  |  |
| Creatinine (mg/dL) |  |  | D-dimer (mg/L) |  |  |
| RBS |  |  | HbA1C |  |  |
| Others |  |  |  |  |  |

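### Pregnancy is an exclusion and every active arm gives ribavirin for 10 days, but the scheduled baseline investigations include no pregnancy test

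*Protocol*

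**What the plan says.** Under item (e) of the Protocol, Exclusion criteria, the fifth criterion excludes "Pregnant or breastfeeding females". Adults of both sexes from age 18 may enrol.

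The flow diagram and Treatment Schedule in the same item define five arms. Two are standard treatment alone. The other three (non-severe B, severe B and severe C) each contain ribavirin, as a 2.4 g loading dose and then 1.2 g every 12 hours, for 10 days.

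The Design paragraph says of the enrolment data: "It will be documented along with investigations including CBC, ECG, LFT, RFT, G6PD status". The table under Timelines of investigations sets the baseline tests that are repeated every 72 hours. Its only open-ended row is "Other organ markers as per involvement".

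A non-severe patient who does not improve or becomes severe may be randomised a second time, into the severe group, after new consent. No further eligibility test is named at that step.

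The case report form has a pregnancy item under Demographics: "Pregnant? ☐Yes ☐No ☐Unknown ☐N/A If yes: Gestational weeks assessment".

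**The concern.** The exclusion is absolute. The third and fourth criteria, on contraindications and allergy, are limited to what is already known. The fifth has no such limit, so it covers a pregnancy of which the woman is unaware. Applying it needs a test, because history alone cannot find such a pregnancy. In the severe group history may not be available at all, since that group includes ventilated patients and patients in septic shock.

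If the investigations are run as listed, a woman whom the protocol means to keep out can be randomised to an active arm and given ribavirin. No later test is named, so nothing scheduled would interrupt the 10-day course. What is at stake is the safety of the woman and the fetus. Randomisation, the estimates and the analysis are unaffected.

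**Working it through.** The plan gives no figure to reproduce, so the check sets its lists side by side.

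1. **Who can be enrolled.** Women aged 18 or over, with pregnancy and breastfeeding excluded (item (e), inclusion and exclusion criteria).

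2. **What the active arms give** (item (e), Treatment Schedule). Non-severe B is hydroxychloroquine plus ribavirin. Severe B is the same combination. Severe C is lopinavir-ritonavir plus ribavirin. Count: 3 of 3 active arms contain ribavirin.

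3. **Enrolment investigations** (item (e), Design). Five are named: CBC, ECG, LFT, RFT and G6PD. Pregnancy tests: 0 of 5.

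4. **Baseline table** (item (e), Timelines of investigations). There are eleven rows: CBC; LFT; KFT; HbA1c and blood sugar; RT-PCR; PT/INR; electrolytes; ABG; chest X-ray; ECG; other organ markers. Pregnancy tests: 0 of 11. The last row is open but is tied to organ involvement, so it does not order a pregnancy test.

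5. **Supporting lists.** The budget list names ECG, LFT, KFT, CBC and "Others specific marker of an organ involvement". The case report form page headed "LABORATORY RESULTS ON ADMISSION" has no pregnancy-test field; its only urine item is routine microscopy, and it ends with a blank row for other results. The follow-up laboratory pages are the same in this respect. These lists agree with steps 3 and 4 but add little, because they also omit tests that the protocol clearly orders (see the objection).

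6. **Second randomisation.** A woman first allocated to non-severe standard treatment has had no ribavirin. If she is shifted and re-randomised, a draw of severe C starts it. The text sends a draw of the HCQ arm to institute treatment; it is unclear whether that applies to everyone or only to patients already given HCQ. On either reading, severe C can be her first exposure, and no test comes before it.

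Steps 3 and 4 carry the argument: the two places that order tests before randomisation contain none that detects pregnancy.

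**The case against.** The strongest reply is that silence in a list is not proof. The enrolment sentence is worded as a list of examples. G6PD is ordered there but is missing from the table, the budget and the laboratory forms. RT-PCR, chest X-ray, ABG and PT/INR are in the table but are not named in the budget. An unlisted test might be done as routine care. The information and consent pages are not in the public copy, and the visible case report form appears to start part-way through, so an eligibility check could sit on a missing page. All of this stands as a limit on what can be claimed. It does not supply an order for the test, and the schedule, which spells out tests as basic as a blood count, is where that order belongs.

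A second reply is that no visible text describes a fetal risk of ribavirin. That is true, and the point does not rely on one. It rests on the protocol's own decision to exclude pregnant women from a trial whose active arms all contain the drug. Some arm labels in the case report form leave ribavirin out, but the objectives, flow diagram and Treatment Schedule include it; that mismatch is a separate matter.

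A reader might also infer four stronger things, which the document does not support:

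- *That the case report form permits enrolment with unknown or positive status.* The item is a demographics field, not an eligibility checklist. The form's medication page also allows an unknown answer for drugs covered by other exclusions. Eligibility is set by the criteria and the screening step.
- *That section F contradicts the exclusion.* Declaring no vulnerable subjects and leaving "Pregnant Women [ ] Children [ ] Elderly [ ] Foetus" unticked is consistent with excluding pregnant women.
- *That the chance of drawing a ribavirin arm measures the harm.* The allocation ratio is not stated, and such a percentage says nothing about how many pregnancies would be missed.
- *That QT prolongation has the same gap.* An ECG is ordered at enrolment, and prolongation seen on it is then known and falls under the third criterion.

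**Conclusion.** The point holds in a limited form. The protocol sets an unqualified pregnancy exclusion and then schedules baseline tests that cannot enforce it for an unrecognised pregnancy. In the visible schedule the gap is complete, and it recurs at the second randomisation.

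The size in patients cannot be given: the document has no sample size, no expected share of women of childbearing age and no pregnancy rate.

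The conclusion assumes that the visible schedule governs which tests are done before allocation, and that no missing page orders the test. If one does, the remaining work is to bring the schedule into line with it. The gap should be closed because the remedy is cheap and the exposure could not be undone. It gives no reason to doubt the trial's comparisons.

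**What to change.** - Add a pregnancy test for women of childbearing potential to the enrolment investigations and to the baseline column of the investigation table.
- State that a negative result is required before randomisation, and that positive or unknown status means not eligible.
- Before any second randomisation into the severe group, confirm that the result is on file.
- As a minor matching edit, add a result field to the admission laboratory page and align the demographics item with the new rule.

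Section H already provides for 6 ml of blood at each draw. The test can use that sample, assuming the volume suffices for one more assay. The cost is one routine test per eligible woman, one line in the table, a small form edit and a short delay before allocation while the result is read.
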